| Medication adherence | 
Self-reported medical adherence is measured by Morisky Green Levine Scale separately for anti-hypertensive medicine, aspirin and statins if the participant was taking the medicine. A score ranged from 0 to 4 are calculated by summing all coded answers where lower scores correspond to better medication adherence.
                                                                                                                                                                                                                                                                                                                                                                                                                                                              | The variable will be dichotomized as high adherence (0) vs. low to medium adherence (1-4).             |

---

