| 
2.1 Medication adherence:
 
2.1a Did the patient forget to take medicine?  1 Yes  0 No
 
2.1b Have the patient paid less attention to taking medicine?  1 Yes  0 No
 
2.1c When the subjective symptom improves, whether the patients stopped medication?  1 Yes  0 No
 
2.1d When the subjective symptom deteriorates, whether the patients stopped medication?  1 Yes  0 No
 
2.1e Fill in the following according to the patient medication record: the total number of days patients adhere to take medicine from the last visit to this follow-up _____ days
 
2.1f Please upload the medication record chart of the patient [picture]
 
2.1g Main reasons leading to not adhering to take medication:
 
 1 Doctor's suggestions  2 Too expensive  3 Forget to take medication  4 Not effective
 
 5 side effect  6 Other
                                                                                                                                                                                                                                                                                                                                                                                                                                                                          |

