## 3.3 Outcomes evaluation and measurement

The outcomes for follow-up assessment will be in the same way of the baseline and 12-month follow-up assessment. Table B-1 illustrate all the key aspects of measurement by comparing with baseline and 12-month follow-up assessment.

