2885 Ob Please enter the value of the first blood pressure measurement for diastolic pressure (low  
2886 pressure): \_\_\_\_\_mmHg

2887

2888 **P: DRUG USE - ASPIRIN**

2889 P1. Are you taking anti-platelet (aspirin) medication?

2890 Yes No(Jump to lipid-lowering drugs)

2891 P2. Drug classes

2892 Aspirin Bayaspirin Clopidogrel Dipyridamole

2893 Cilostazol Ozagrel Other\_\_\_\_\_

2894 For this type of medicine:

2895 P3a. When did you start taking this medicine?

2896 Within 6 months

2897 Within 6 months to 1 year

2898 1 to 3 years

2899 More than 3 years

2900 P3b. How many months in the past year have you been taking the drug? \_\_\_\_\_ months

2901 P4. How many days in the past two weeks have you been taken the drug? \_\_\_\_\_ days

2902 P5. Did you take the medicine today? Yes No

2903 P6. Did you sometimes forget to take your medication? Yes No

2904 P7. Did you ever fail to take your medication? Yes No

2905 P8. Did you sometimes stop taking your medication when you feel your symptoms are getting better?

2906

2907 Yes No

2908 P9. Have you reduced or stopped taking your medication on your own without informing your doctor because you felt worse after taking it?

2909

2910 Yes No

2911 P10. Why did you not take it as prescribed by your doctor?

2912 ☐ The medication is too expensive

2913 ☐ I forget to take it

2914 ☐ It doesn't work

2915 ☐ There are side effects

2916 ☐ I'm worried about side effects

2917 ☐ I don't feel I need to take it every day and can stop when my symptoms improve

2918 ☐ I think I'm taking too much medication in a day

2919 ☐ I'm on other medication

2920 ☐ I'm out of medication (lack of medication)

2921 ☐ I don't want to take it

2922 ☐ Other reasons (please specify) \_\_\_\_\_

2923

2924 **Q: DRUG USE - LIPID-LOWERING DRUGS**

2925 Q1. Are you taking lipid-lowering statins?

2926 Yes No

2927 Q2. Drug classes

2928 Simvastatin Pravastatin Atorvastatin Other\_\_\_\_\_

2929 For this type of medicine:

2930 Q3a. When did you start taking this medicine?

2931 Within 6 months

2932 Within 6 months to 1 year

2933 1 to 3 years

2934 More than 3 years

2935 Q3b. How many months in the past year have you been taking the drug? \_\_\_\_\_ months

2936 Q4. How many days in the past two weeks have you been taken the drug? \_\_\_\_\_ days

2937 Q5. Did you take the medicine today? Yes No

2938 Q6. Did you sometimes forget to take your medication? Yes No

2939 Q7. Did you ever fail to take your medication? Yes No

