2940 Q8. Did you sometimes stop taking your medication when you feel your symptoms are getting

2941 better?

2942 Yes No

2943 Q9. Have you reduced or stopped taking your medication on your own without informing your

2944 doctor because you felt worse after taking it?

2945 Yes No

2946 Q10. Why did you not take it as prescribed by your doctor?

2947 ☐ The medication is too expensive

2948 ☐ I forget to take it

2949 ☐ It doesn't work

2950 ☐ There are side effects

2951 ☐ I'm worried about side effects

2952 ☐ I don't feel I need to take it every day and can stop when my symptoms improve

2953 ☐ I think I'm taking too much medication in a day

2954 ☐ I'm on other medication

2955 ☐ I'm out of medication (lack of medication)

2956 ☐ I don't want to take it

2957 ☐ Other reasons (please specify) \_\_\_\_\_

2958

2959 **R: DRUG USE - ANTIHYPERTENSIVE DRUGS**

2960 R1. Are you taking antihypertensive drugs?

2961 Yes No

2962 R2. Drug classes

2963 Nifedipine Extended release nifedipine tablets Nitrendipine Amlodipine

2964 Enalapril Captopril Hydrochlorothiazide Indapamide Compound reserpine tablets

2965 Lacidipine Felodipine Sustained-release Tablets Levoamlodipine

2966 Benazepril Fosinopril Lisinopril Losartan Telmisartan

2967 Irbesartan Valsartan Atenolol Metoprolol Bisoprolol

2968 Compound Dibazol hydrochlorothiazide capsules Propranolol hydrochloride tablets

2969 Compound Hypotensive Tablets Others\_\_\_\_\_

2970 For this type of medicine:

2971 R3a. When did you start taking this medicine?

2972 Within 6 months

2973 Within 6 months to 1 year

2974 1 to 3 years

2975 More than 3 years

2976 R3b. How many months in the past year have you been taking the drug? \_\_\_\_\_ months

2977 R4. How many days in the past two weeks have you been taken the drug? \_\_\_\_\_ days

2978 R5. Did you take the medicine today? Yes No

2979 R6. Did you sometimes forget to take your medication? Yes No

2980 R7. Did you ever fail to take your medication? Yes No

2981 R8. Did you sometimes stop taking your medication when you feel your symptoms are getting  
2982 better?

2983 Yes No

2984 R9. Have you reduced or stopped taking your medication on your own without informing your  
2985 doctor because you felt worse after taking it?

- 2986    Yes No
- 2987    R10. Why did you not take it as prescribed by your doctor?
- 2988    ☐ The medication is too expensive
- 2989    ☐ I forget to take it
- 2990    ☐ It doesn't work
- 2991    ☐ There are side effects

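### The second adherence item in the Part B form has no recall window, matches no adherence item printed in Part A, and can largely decide the binary adherence outcome

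*Combined protocol and SAP*

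**What the plan says.** Part B Appendix B2 asks four yes/no adherence questions for each drug class. For aspirin they are "P6. Did you sometimes forget to take your medication", "P7. Did you ever fail to take your medication", "P8. Did you sometimes stop taking your medication when you feel your symptoms are getting better" and "P9. Have you reduced or stopped taking your medication on your own without informing your doctor because you felt worse after taking it". The statin block (Q6 to Q9) and the antihypertensive block (R6 to R9) use the same wording, including "R7. Did you ever fail to take your medication". None of the second items carries a recall period.

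Part B section 3.3 opens with the statement "The outcomes for follow-up assessment will be in the same way of the baseline and 12-month" follow-up. Section 3.3.2 and Table B-1 name the 4-item Morisky Green Levine Scale, as does Part A section 5.7. Part A Table 4 sums the answers to a score from 0 to 4, separately for antihypertensives, aspirin and statins among those taking the drug, and then sets the cut: "The variable will be dichotomized as high adherence (0) vs. low to medium adherence (1-4".

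Part A prints two other adherence item sets. The participant survey (Appendix A-3) contains an eight-item Morisky scale. The village doctors' follow-up record (Appendix A-2) has four items, the second being "Have the patient paid less attention to taking medicine"; the Chinese app screen in the same appendix also asks about inattention.

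**The concern.** Medication adherence is among the stated aims of Part B and is one of its secondary outcomes. Under the cut at 0, one yes moves a participant out of the high-adherence group. An item that asks about any failure at any time is easier to answer yes than one about the last two weeks or one about carelessness. Read literally, it also reaches back before randomization. Participants had prevalent stroke, and the form has an open-ended category for users of more than three years, so a lapse before baseline could bar a participant from a score of 0 whatever the later behaviour.

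Three things are at stake. The outcome may separate good from poor current adherence less well. The baseline value used as a covariate under Part B section 3.4.1 may have been collected with a different item. And the proportion with high adherence cannot safely be set beside the baseline and 12-month proportions.

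**Working it through.** The plan gives no figure for this outcome that could be reproduced, so the check is of wording and scoring.

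**1. Wording, side by side**

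| Part B item (aspirin) | Nearest item in Appendix A-3 | App record in Appendix A-2 |
|---|---|---|
| P6: forgetting | Item 1: forgetting | 2.1a: forgetting |
| P7: ever failing to take, no window | Item 2: days missed for causes besides forgetting, preceding two weeks | 2.1b: attention to taking medicine |
| P8: stopping when better | Item 6: stopping when symptoms are controlled | 2.1c: stopping when better |
| P9: reducing or stopping when worse | Item 3: cutting back or stopping when worse | 2.1d: stopping when worse |

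Three of the four Part B items have a close counterpart in both Part A sets. P7 does not. Compared with A-3 item 2 it lacks both the two-week window and the exclusion of forgetting. Compared with 2.1b it asks about something else.

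**2. Scoring**

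Four yes/no items give 2^4 = 16 patterns. High adherence is the single pattern with no yes. Count the patterns in which the binary result equals the answer to P7 alone.

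- If forgetting (P6), stopping (P8) and reducing or stopping (P9) each imply a failure to take the drug, a no to P7 forces no to the others. Consistent patterns: 8 with P7 yes, plus 1 with P7 no, giving 9. Agreement with P7 alone: 9 of 9.
- If reducing under P9 is not counted as a failure to take, P9 can be yes while P7 is no. Consistent patterns: 8 + 2 = 10. Agreement: 9 of 10, the exception being a yes to P9 only.
- If answers need not be consistent, agreement is 8 + 1 = 9 of 16.

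**3. Effect on the proportion with high adherence (assumptions; no value is in the documents)**

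Suppose a bounded item would class 50% to 80% of users as high adherence, and the unbounded item turns 10% to 50% of those to yes. The proportion becomes base x (1 - f). Lowest: 0.50 x 0.50 = 25%. Highest: 0.80 x 0.90 = 72%.

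If the same fraction f is lost in both arms, the risk difference becomes (1 - f)(p1 - p0). It shrinks by 10% to 50%. The risk ratio is unchanged in expectation but rests on fewer high responders.

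**4. Effect of the length of the window (assumptions)**

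If a user misses at least one dose in a given month with probability p, independently across months, the share who can answer no over m months is (1 - p)^m.

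| p | 1 month | 12 months | 36 months | 54 months |
|---|---|---|---|---|
| 5% | 95% | 54% | 16% | 6% |
| 2% | 98% | 79% | 48% | 34% |

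The result depends heavily on p, which the documents do not supply. The table shows only that the window matters.

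**The case against.** The strongest reply is that no change of item can be proved. The four-item wording administered at baseline and 12 months is not printed. The app record is an intervention tool for intervention-arm village doctors, and Part A section 6.1 assigns its data mainly to project management and process evaluation. It is not the outcome instrument. The outcome survey prints eight items, which itself disagrees with the named 4-item scale. This stands: a reader might infer that Part B abandoned the scale used in the trial, but the documents do not show which four items were used.

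Second, Appendix B2 appears only in English and its English is loose in places, so P7 may be a poor rendering of an attention item. The documents cannot settle this.

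Third, missing windows are not unique to P7. Items 2.1a to 2.1d of the app record have none, and A-3 item 3 asks about ever cutting back or stopping. The window arithmetic would apply to any unbounded item under a cut at 0. That is fair. P7 still stands out, because it is the broadest item and its nearest outcome-survey counterpart is bounded.

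Fourth, four items are still asked and summed, and respondents may answer inconsistently. A reader might infer that the outcome collapses to one question. The 9 of 16 count shows that this needs consistent answers.

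Finally, both arms receive the same form from blinded assessors, so the wording does not by itself favour an arm. This also stands.

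**Conclusion.** The concern holds in a limited form. The printed second item in P7, Q7 and R7 is unbounded in time and matches no adherence item printed in Part A, although Part B promises the same measurement and names the same 4-item scale. With the cut at 0, it can largely decide the binary outcome for respondents who answer consistently: 9 of 9 or 9 of 10 patterns, depending on how reducing a drug is read.

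The likely harm is weaker discrimination, a less informative baseline covariate and levels that are not comparable over time, in one of several secondary outcomes. The size is unknown. It might be tempting to conclude that nearly all long-term users would fall out of the high-adherence group, but that rests on an assumed monthly rate; at 2% per month, 34% would still qualify after 54 months. The verdict takes the English form as a faithful record of what is asked. If it is a loose translation, documenting the administered text would resolve the wording mismatch.

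**What to change.** Set P7, Q7 and R7 to the exact second-item wording and recall window administered at baseline and 12 months. State that wording for each visit, and reconcile the app record in Appendix A-2, the eight-item block in Appendix A-3 and the Part B blocks with the named 4-item scale. S7, in the glucose-lowering block, is outside the adherence outcome defined in Table 4 and needs no change for this purpose.

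If data have already been collected with the printed wording:

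- keep the 4-item score and its cut as defined;
- add a sensitivity analysis without item 7, using P6, P8 and P9 and the Q and R equivalents;
- report days taken in the past two weeks (P4, Q4, R4) as a supporting measure, which the form already collects;
- do not compare the level of the 4-item outcome across time points.

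The cost is one reworded item for each of three drug classes, or a short addition to the analysis plan with a little extra analysis. The downside is that the three-item version is not a validated scale, so it should stay a sensitivity analysis.

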### 3077 5.3 Appendix B3. Interview outline for SINEMA long-term follow-up

#### 3078 Interview guide for patients

3079 **Introduction:** Thank the participant for their time and explain the purpose of the interview.

3080 Clarify that their participation is voluntary and their responses will be kept confidential.

3081 Obtain consent for recording the interview.

3082

3083 **Step 1: Building Rapport:** Begin with light conversation to make the participant feel comfortable.

3084 Share your interest in understanding their personal experience with the SINEMA intervention.

3085

#### 3086 **Step 2: Conducting the Interview**

3087 **\*\*Question 1: Stroke Experience and Health Management Post-Intervention\*\***

3088 - Since the SINEMA intervention ended, could you describe how you've been managing your  
3089 health and any specific stroke-related care you've continued?

3090 - Are there any particular habits or practices recommended during the intervention that you've  
3091 maintained? Why do you think you've continued these?

3092 **\*\*Question 2: Continued Practices from Intervention\*\***

3093 - Has the SINEMA intervention led to any long-lasting changes in your daily routine, especially  
3094 regarding your stroke management?

3095 - What advice or aspects of the intervention have you found most valuable and continue to use?

3096 **\*\*Question 3: Support Systems\*\***

3097 - What kind of support do you feel is essential for you to continue managing your health  
3098 effectively? This could be from healthcare providers, family, community, etc.

3099 - Can you give examples of how your family or community has supported you in maintaining the  
3100 health practices initiated during the SINEMA intervention?

3101 **\*\*Question 4: Medication Adherence Post-Intervention\*\***

3102 - How do you manage your medication schedule now that the intervention has ended? Have  
3103 you faced any challenges with this?

3104 - If the daily voice messages or handouts were discontinued after a year, how did that affect  
3105 your medication adherence?

3106 **\*\*Question 5: Communication Preferences\*\***

3107 - After the intervention, what has been your preferred method of receiving health information  
3108 and why?

3109 - How effective do you find different forms of communication, like text messages, voice  
3110 messages, or direct conversations with healthcare providers, in helping you manage your health?

3111 **\*\*Question 6: Impact of COVID-19\*\***

3112 - How has the COVID-19 pandemic affected the way you manage your health, particularly in  
3113 relation to stroke management?

3114 - What adaptations have you made to your health management routine as a result of the  
3115 pandemic?

3116 **\*\*Question 7: Lifestyle Changes and Health Behaviors\*\***

3117 - Apart from medication adherence, what lifestyle changes have you implemented since the  
3118 intervention? This can include diet, exercise, smoking cessation, etc.

3119 - How sustainable have these lifestyle changes been, and what do you think has contributed to  
3120 your adherence to these changes?

3121 **\*\*Question 8: Additional Feedback and Suggestions\*\***

3122 - Reflecting on the SINEMA intervention, is there anything you would have liked to be done  
3123 differently?

3124 - Do you have any suggestions for additional support or resources that would help you or other  
3125 stroke patients manage their health better?

3126

3127 **Step 3: Conclusion**

3128 - Reiterate your thanks and ask if they have any final thoughts to share.

3129 - Provide contact information for any further questions or support they might need.

3130 - Assure them that the feedback they've provided will be invaluable in enhancing the SINEMA  
3131 intervention for future participants.

3132

3133 Based on the provided outline and additional information, here is a revised and detailed interview guide  
3134 tailored for village doctors (VDs), township, and county managers:

3135

3136 [Interview guide for VDs, township and county managers](#)

3137 **Introduction:** Thank you for your dedication and contribution to the SINEMA study. This  
3138 interview aims to gather your insights on the SINEMA intervention model and the associated  
3139 mobile application you have used. Your feedback is critical to refining our approach to better  
3140 serve stroke patients in rural China.

3141

3142 **Consent:**

3143 - Explain the interview process, confidentiality measures, and how the data will be used.

3144 - Confirm that the participant consents to the interview and its recording.

3145

3146 **Step 1: Rapport Building**

3147 - Begin with an informal conversation to establish a comfortable atmosphere.

3148 - Show genuine interest in their professional experiences and roles in the SINEMA intervention.

3149

3150 **Step 2: Detailed Interview Questions**

3151 **\*\*Question 1: Stroke Management Challenges\*\***

3152 - Reflecting on your experience, what are the primary challenges you face in stroke prevention

3153 and management within primary healthcare settings?

3154 - How well do you think the national basic public health services cater to the needs of secondary

3155 stroke prevention?

3156 **\*\*Question 2: Comparing SINEMA App with National Health Service System\*\***

3157 - In contrast to the traditional national public health service system, what benefits or challenges

3158 has the SINEMA App presented?

3159 **\*\*Question 3: Training Efficacy and Content\*\***

3160 - Can you describe the impact of the training on your medical knowledge and practices?

3161 - Which parts of the training were most beneficial, and which could be improved or omitted?

3162 - Are there crucial topics that the training did not cover that you feel should be included?

3163 **\*\*Question 4: Follow-up Visits and Patient Management\*\***

3164 - How did you organize the follow-up visits with the patients? Were these conducted at clinics or

3165 at the patients' homes?

3166 - Could you describe the integration of the follow-up visits with your regular duties?

3167 - What is your perspective on the workload? Is the frequency and duration of the intervention

3168 feasible for you to manage?

3169 **\*\*Question 5: Medication Adherence Monitoring\*\***

3170 - How do you assess and ensure medication adherence among your patients?

3171 - What methods do you use to measure their blood pressure, and how often?

3172    **\*\*Question 6: SINEMA App Usability and Impact\*\***

3173    - Share your experience with learning and using the SINEMA App.

3174    - Has the App facilitated better patient management, or has it introduced new complexities?

3175    - Could you provide any suggestions for improving the App's design and functionality?

3176    **\*\*Question 7: Performance, Compensation, and Support Systems\*\***

3177    - What key performance indicators do you believe would effectively measure the success of  
3178    interventions like SINEMA?

3179    - Discuss the compensation structure and whether it aligns with your expectations and workload.

3180    - Evaluate the support provided by the township hospital managers. Are there ways this support  
3181    could be enhanced?

3182    **\*\*Question 8: Communication Tools and Peer Support\*\***

3183    - How effective is the WeChat group in fostering communication and support among healthcare  
3184    providers involved in the SINEMA intervention?

3185    **\*\*Question 9: Long-term Adaptations and Sustainability\*\***

3186    - Since the official SINEMA intervention period has concluded, what strategies have you  
3187    employed to sustain its practices and principles in your routine healthcare services?

3188    - Can you describe any modifications you have made to the intervention's methods to better fit  
3189    the local context or to address any barriers that have arisen over time?

3190    - In terms of the technologies and methods introduced by SINEMA, which do you believe have  
3191    the potential for long-term integration into your health management practices?

3192    - How do you foresee the continuation of these health practices without the direct support of the  
3193    SINEMA program, particularly in terms of resources and training?

3194    - What additional tools, resources, or changes in policy would you consider essential to ensure  
3195    the ongoing success and sustainability of the practices introduced by the SINEMA intervention?

3196    **\*\*Question 10: Additional Feedback\*\***

3197    - Is there any other feedback or suggestions you would like to share that we haven't covered?  
3198

3199    **Step 3: Conclusion**

3200    - Thank the interviewee for sharing their valuable insights and contributing their time.

3201    - Hand over a small token of appreciation to show gratitude for their participation.

3202    - Ensure the interviewee knows how to contact you for any follow-up questions or further  
3203    information.

3204 - Close the conversation by reiterating the importance of their feedback to the improvement of  
3205 the SINEMA project.

3206

3207

3208

3209

3210

3211

3212

